#### Primary outcomes: MRI brain measures

Assessment will comprise the following MRI brain measures. Anatomical MRI: measures of cortical thickness at all points across the cerebrum. Resting State Functional MRI (rsfMRI): measures of functional connectivity throughout the brain. Cyberball Task-Related Functional MRI (fMRI): measures of brain activation throughout the brain in response to trust, mistrust (social exclusion), and rebuilding of trust (social re-inclusion). Diffusion Tensor Imaging (DTI): measures of fractional anisotropy and average diffusion coefficient.

What these outcomes tell us about the brain MRI is an entirely safe way of imaging the brain at any age. It is routinely performed in unsedated people at multiple time points, including multiple time points within an RCT, and without the need for exposure to any radioactivity. MRI scanning can be performed in different modes, with each modality providing unique information probing different aspects of the brain’s structural and functional organization. *Anatomical MRI* provides information about brain structure, most commonly the volumes and shapes of particular brain regions. *Diffusion Tensor Imaging (DTI)* provides information about tissue organization within the brain, especially white matter fibers that connect one brain region to another. At each voxel, Fractional Anisotropy (FA) measures the directional diffusion of water, Mean Diffusivity (MD) measures the overall diffusion of water, Axial Diffusivity (AD) measures diffusion along the long axis of diffusion, which is presumed to be along the long axis of the fiber bundle, and Radial Diffusivity (RD) measures diffusion perpendicular to the long axis of diffusion or fiber bundle. *Functional MRI (fMRI)* provides measures of time-dependent changes in the relative concentration of deoxyhemoglobin within each voxel, which itself is driven largely by changes in oxygen use and the underlying changes in neuronal activity within the voxel [87, 88]. Measures of *resting state connectivity (rsfMRI)* are in essence measures of cross-correlation for the fMRI series of two different voxels (i.e., two different points in the brain), which assesses how strongly those two regions communicate with one another over time.

##### MRI Scanning

All scans will be acquired on 3.0 T scanners: Siemens Prisma (Frankfurt, Lausanne), Philips Achieva (CHLA). Signal-to-noise and contrast-to-noise was determined to be comparable across all scanning platforms (Tables 4, 5, 6 and 7).

**Table 4 Tab4:** Anatomical MRI

Scan Parameters for 3.0T MRI Scanners	Siemens	Philips
Coil	64	32
Sequence	MPRAGE	3D Gradient Echo Turbo Field Echo factor = 130
Scan plane	Sagittal	Sagittal
Direction of frequency coding	H-F	S/I
Echo time	2.75 ms	2.8 ms
Inversion Preparation Time	920 ms	920 ms
Flip Angle	9	9
Bandwidth	190 Hz/pixel	206 Hz/pixel
Repetition time (or MPRAGE TR)	2000 ms	3000 ms
Field of View	256 mm	256 mm
Matrix	256 × 256	256 × 256
Slice thickness	1.0 mm 176 slices	1.0 mm 176 slices
Phase Field of View	1.0	1.0
Number of excitations	2	2
Time	9 min, 20 secs	9 min, 3 secs

**Table 5 Tab5:** Task-based fMRI: cyberball

Sequence	2D Gradient Echoplanar	2D Gradient Echoplanar
Scan plane	Axial Oblique, parallel to the AC-PC line	Axial Oblique, parallel to the AC-PC line
Effective Echo time	34 ms	34 ms
Flip Angle	90^o^	90^o^
Repetition time	4630 ms	4630 ms
Field of View	24 cm	24 cm
Matrix	112 × 112	112 × 112
Slice thickness	2.4 mm	2.4 mm
Number of Volumes/Run	215	137
In-Plane Resolution	24 cm/112 × 24 cm/112 = 2.14 × 2.14 mm2	24 cm/112 × 24 cm/112 = 2.14 × 2.14 mm2
Number of Slices	60	60
Number of Runs	1	1
Time	16 min 40 s (1000 s)	10 min 34 s (643 s)

**Table 6 Tab6:** Resting-State fMRI

	**Siemens**	**Philips**
Sequence	2D Gradient Echoplanar	2D Gradient Echoplanar
Scan plane	Axial Oblique, parallel to the AC-PC line	Axial Oblique, parallel to the AC-PC line
Echo time	34 ms	34 ms
Flip Angle	90^o^	90^o^
Repetition time	4630 ms	4630 ms
Field of View	24 cm	24 cm
Matrix	112 × 112	112 × 112
Slice thickness	2.4 mm	2.4 mm
Number of Volumes/Run	90	90
In-Plane Resolution	24 cm/112 × 24 cm/112 = 2.14 × 2.14 mm2	24 cm/112 × 24 cm/112 = 2.14 × 2.14 mm2
Number of Slices	60	60
Number of Runs	1	1
Time	7 min 11 s (1000 s)	7 min 11 s (1000 s)

**Table 7 Tab7:** Diffusion tensor imaging

	**Siemens**	**Philips**
Sequence	2D Gradient Echoplanar	2D, single-shot, echo-planar imaging
Scan plane	Axial Oblique, parallel to the AC-PC line	Axial Oblique, parallel to the AC-PC line
Echo time	66 ms	66 ms
Flip Angle	90^o^	90^o^
Repetition time	7300 ms	7700 ms
Field of View	24 cm	24 cm
Matrix	112 × 112	112 × 112
Slice thickness	2.0 mm	2.0 mm
Acceleration factor	2 (GRAPPA)	2 (ASSET)
Number of DWIs	64	64
In-Plane Resolution	24 cm/112 × 24 cm/112 = 2.14 × 2.14 mm^2^	24 cm/112 × 24 cm/112 = 2.14 × 2.14 mm^2^
Number of Slices	72	72
Number of Runs	2	2
b-values	0, 1000 s/mm^2^	0, 1000 s/mm^2^
Time	8 min 46 s	About 7 min

##### Theoretical basis for the fMRI task used in MODE

Chronically depressed patients need to experience an intensive, professional, reliable, holding, and containing therapeutic relationship in order to both regain confidence in a "helping object" in the form of the therapist and develop a basic feeling of self-agency. According to psychoanalytic theory, severe early life trauma produces a defensive withdrawal of the self from outside objects into a depressed inner world. Metaphorically speaking, the self is encapsulated in an inner crypt [89]. Therefore, as a first indispensable step in a therapeutic relationship, the withdrawn, depressed patient must regain confidence in an external object (i.e. the therapist) to dare to confront himself with the traumatic experiences in the transference relationship, in the hope of making alternative, "healing" experiences. The fMRI task we have selected and adapted for use in MODE is intended to index the development of this basic trust in others in response to the therapeutic interventions.

##### Task-based fMRI ‘Cyberball’ paradigm

MODE will study the neurobiological mechanisms that subserve this evolving sense of interpersonal trust within patients over the first year of psychoanalytic therapy. We have adapted a task that participants perform while in the MRI scanner so as to identify the brain systems that support the cognitive, emotional, and behavioral requirements of the task. This fMRI task, called “Cyberball” [90], is a computer game in which participants believe they are playing with real people in another room of the building. It is designed to manipulate the independent variable of social exclusion, via including and then suddenly excluding the participant in the ball-tossing. The game begins with the participant and two other “players” throwing a ball to one another, each of the three players receiving it an equal number of times. Without warning, the other two players then stop throwing the ball to the study participant, an experience that has been shown to produce feelings of betrayal and social exclusion. After some time, they once again throw the ball to the study participant, which produces feelings of relief upon re-inclusion. Brain activity during each of the three phases of this fMRI task will be measured at study baseline and after one year of psychoanalytic therapy [91–93]. Our aim is to identify the neural systems that support the expression of trust, mistrust, and social exclusion, and then reintegration of trust in interpersonal relationships, how activity in these systems change over the year in depressed patients compared with the change observed in healthy controls, and how high vs low frequency of PA therapy modifies activity in these systems over time.

#### Secondary outcome measures

MODE will investigate whether and how brain changes are associated with common measures of change for patients with chronic depression and early trauma after one year of treatment. To achieve this aim and as recommended in meta-analytic reviews, various broad areas of patient’s functioning are assessed including (1) psychopathology, (2) personality, social and work functioning, and (3) dynamic functioning which may underlie impaired functioning and contribute to vulnerability to psychiatric disorders [94]. Due to their depressive symptomatology, patients may face some difficulties with self-report questionnaires. Therefore, we have restricted the total number of items included in the assessment battery (Table 8).

**Table 8 Tab8:** Secondary outcomes: clinical response measures

Clinical therapeutic outcomes	Clinical-psychoanalytical outcomes
• Beck Depression Inventory (BDI)	• Operationalized Psychodynamic Diagnostics self-report questionnaire (OPD-SQ)
• Depressive Experience Questionnaire (DEQ)	• The Social Cognition and Object Relations Scale-Global Rating Method (SCORS-G)
• Social Functioning Global Assessment of Functioning (GAF)	• Reports of trauma memories (Pennebaker)
• Work Ability Index (WAI)	
• Therapeutic alliance Working Alliance Inventory (WAI-SRp)	
• Inventory of Interpersonal Problems (IIP)	

##### Assessment of psychopathology

###### Diagnosis

The Structured Clinical Interview for DSM (SCID, [95]) is used to collect diagnostic information. This instrument enables the collection of extensive information on psychiatric conditions including mood and anxiety disorders.

###### Depression

Depressive symptoms will be assessed using three instruments: (1) The Inventory of Depressive Symptom (QIDS; [96]), a clinician rating measure (QIDS-C_16_); (2) the self-rated version of the QIDS (QIDS-SR_16_), 16-item measures of depressive symptoms; and (3) the Berg -Depression Inventory (BDI-II; [97]). The Depressive Experience Questionnaire (DEQ; [98]), which assesses a wide range of life experiences often reported by depressed individuals but not considered symptoms of depression.

###### Distress

The Symptom Check-List (SCL-90-R; [99]) is a widely used self-report measure of distress and psychiatric symptoms.

###### Early life trauma

Early childhood trauma is recognized as one of the best predictors of response to psychotherapy for severely depressed patients ( [100]). The Childhood Trauma Questionnaire Short-Form (CTQ-SF; [101]) provides a quick, multidimensional, retrospective measure of childhood trauma with good reliability and validity.

###### Patient trauma narratives

Patients will be asked to send a written trauma narrative to the study center with 5 keywords. After the year of study, the research team will send again the keywords to the participant and will ask them to write again their memories on trauma. The trauma narrative will be written freely, with the instruction to write about their deepest thoughts and feelings about the most disturbing aspects of their childhood. Participants will be asked to write during 15 to 20 min once started. The Linguistic Inquiry Word Count (LIWC; [102]) will be applied to patient trauma narratives to investigate patient narratives about their central early trauma as well as to their dream diaries [103, 104].

##### Dynamic personality functioning

###### Psychodynamic functioning and change

The Operationalized Psychodynamic Diagnosis (OPD) is a form of multiaxial diagnostic system based on five axes: I = experience of illness and prerequisites for treatment, II = interpersonal relations, III = conflict, IV = structure and V = mental and psychosomatic disorders ( [105]). To measure change in the domain of psychodynamic functioning, we will use the short-form of this questionnaire (OPD-SF, [106]).

###### Dream diary

Dreams will be collected in dream diaries ideally at each follow-up points and latest at study termination with the intent to examine dream characteristics in participants with chronic depression and early trauma. Participants can write freely about their dreams. To help participants document their dreams, an exemplary table will be provided where they can write a description of their dream(s) and report on the feelings they experienced in the dream(s) as well as elements of real life associated to the dream(s). Dream characteristics and changes of the manifest content of dreams as reported in the dream diaries will be assessed using the Social Cognition and Object Relations Scale-Global Rating Method (SCORS-G**;** [107]) as well as the LIWC (see above).

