The prototypical study design in modern medicine for inferring causation is the Randomized Controlled Trial (RCT), which assesses the effects of an experimentally manipulated intervention on the dependent (outcome) variable, usually illness severity. RCTs studying the efficacy and effectiveness of psychotherapy traditionally use clinical measures of symptom change as their primary outcome measure. Many cognitive, behavioral, and neural systems influence symptom severity, however, making these outcome measures very noisy, which in turn reduces the statistical power to detect real change that the therapies produce. Low statistical power in turn necessitates large numbers of participants to detect significant effects of the intervention, thereby increasing the size, duration, and cost of RCTs. Instead of employing change in symptom severity as the usual clinical outcome measure, MODE will use the change in brain imaging measures from the study baseline to study endpoint as the primary study outcome, providing strong causal inference that the treatment causes the changes in brain measures and depressive symptoms observed [80]. In our prior studies using these technologies, brain measures compared with traditional clinical measures provided much more sensitive and robust markers for treatment response, because brain measures are direct reports that the treatments have on the brain, which in turn underlie the change in symptom severity. MODE will be therefore identifying the biomarkers that predict and mediate change in symptoms and other clinical outcomes in high vs low frequency of psychoanalytic therapy in severely and chronically depressed patients.

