#### Secondary hypotheses

##### Psychopathology

Although high and low frequency treatments will both produce clinical improvement, improvement will be significantly greater for high frequency treatment in structural integration (measured with the Operationalized Psychodynamic Diagnosis Structure Questionnaire (OPD-SQ)), depressive symptoms (measured with the BDI-2), and in the manifest dreams (measured with DREams Assessment Scale for measuring Changes in manifest dream (DREAMS-C). Improvement in these clinical measures will associate significantly with the regional changes in MRI measures that change in response to high vs low frequency treatment.

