### Outcome measures

Study participants will be assessed as detailed below and in Table 3, for primary and secondary outcome measures. Patients will be assessed by independent and trained clinicians who are blind to treatment conditions.

**Table 3 Tab3:** Study timetable of assessments

Assessments	Screening	Visit 1	Visit 2	Visit 3	Visit 4	Visit 5
*Description*	*Inclusion*	*Study start*	*FU 3 months*	*FU 6 months*	*FU 9 months*	*Study end*
*Days*	*Day -x*	*Day 0*	*Day 91*	*Day 182*	*Day 273*	*Day 365*
*Window (dates)*			± *7*	± *7*	± *7*	± *3*
*Weeks*		*0*	*13*	*26*	*39*	*52*
Informed consent signed	X					
Eligibility	X					
Demographics		X				
SCID (CI)	X	(X)^a^				X
Psychoanalytic interview	X	(X)^a^				
MRI scan	X	(X)^a^				X
Trust game	X	(X)^a^				X
GAF (Cl)		X				X
BDI-II (SR)	X	X	X	X	X	X
DEQ (SR)		X	X	X	X	X
QIDS (Cl, SR)		X	X (only SR)	X (only SR)	X (only SR)	X
SCL-90-R (SR)		X	X	X	X	X
CTQ (SR)	X					
IIP (SR)		X	X	X	X	X
Work Ability Index (SR)		X	X	X	X	X
OPD_SF (SR)		X	X	X	X	X
Dream Diary (SR)						X
Patient trauma narratives		X				X
WAI-SRp (SR)		Collected each month from Assessment 1 to 5				
Psychotherapy		Throughout study				
Adverse Events			X	X	X	X
SAE		Throughout study				
Medication		X	X	X	X	X

*FU* Follow-up, *Cl* Clinician rated, *SR* Self-reported, *SCID* Structured Clinical Interview for DSM, *GAF* Global Assessment of functioning, *BDI-II* Beck Depression Inventory-II, *DEQ* Depressive Experience Questionnaire, *QIDS* Quick Inventory of Depressive Symptoms (Cl, SR), *SCL-90-R* Symptom Checklist, *CTQ* Childhood Trauma Questionnaire, *IIP* Inventory Interpersonal Problems, *WAI* Work Ability Index, *OPD-SF* OPD structure questionnaire, *WAI-SRp* Working Alliance Inventory, *SAE* Severe Adverse Event

^a^Depending on the availability of the persons concerned, the first MRI examination, the administration of the Trustgame, the SCID interview, and the psychoanalytical interview can take place at the screening visit or visit 1

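### The dream hypothesis concerns improvement and its link to MRI change, but no pre-treatment dream diary is scheduled, so change from baseline is not available for this secondary outcome

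*Protocol article*

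**What the plan says.** The secondary hypothesis headed Psychopathology covers three measures. It expects both arms to improve and then states that "improvement will be significantly greater for high frequency treatment in structural integration", in depressive symptoms on the BDI, and "in the manifest dreams (measured with DREams Assessment Scale for measuring Changes in manifest dream (DREAMS-C"). It adds that "Improvement in these clinical measures will associate significantly with the regional changes in MRI measures" that respond to treatment frequency. Objectives defines the imaging side of that association as "the change in brain imaging measures from the study baseline to study endpoint as the primary study outcome".

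The Dream diary section sets the timing: "Dreams will be collected in dream diaries ideally at each follow-up points and latest at study termination". It also states the aim that "changes of the manifest content of dreams as reported in the dream diaries will be assessed", using SCORS-G and LIWC. In Table 3 the row "Dream Diary (SR") carries a single mark, under Visit 5 (study end, day 365). Table 8 lists SCORS-G among the secondary outcomes and does not list DREAMS-C.

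**The concern.** Improvement is a difference between two times, and the first of them has to precede treatment if the difference is to describe what treatment did. The hypothesis also pairs dream improvement with an MRI change whose first scan is taken before randomisation. If the first dreams are collected after therapy has begun, the dream side of that pair has no starting value.

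At stake are three of the statements made about dreams: that both arms improve, that an individual patient's dreams change from baseline by a measurable amount, and that this amount relates to brain change over the same year. Pre-treatment dreams cannot be collected afterwards, so each patient who starts without a diary is a permanent loss for these analyses, and no later analysis plan can restore them.

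**Working it through.** No sample-size, power or error-rate figure is involved. The check sets the hypothesis against the assessment schedule.

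**1. Reading the Table 3 row.** The columns after the row label are Screening and Visits 1 to 5. The dream diary mark falls in the sixth column, Visit 5. Two other rows confirm the count: the GAF and the patient trauma narratives each show marks at Visit 1 and Visit 5, which agrees with the article's text that trauma narratives are written once and again after the study year.

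**2. Adding the text.** Table 3 labels Visits 2, 3 and 4 as the 3-, 6- and 9-month follow-ups and Visit 5 as study end. The most generous reading of the Dream diary section gives collections at those four times.

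| Source | Screening / Visit 1 | Months 3, 6, 9 | Visit 5 | Total |
|---|---|---|---|---|
| Table 3 | 0 | 0 | 1 | 1 |
| Dream diary section, most generous reading | 0 | 3 | 1 | 4 |

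The baseline count is zero on both. The two sources also disagree with each other, at 1 against up to 4 collections.

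**3. Comparing with other measures.** The BDI-II and the OPD structure questionnaire, which are the other two measures in the hypothesis, are both marked at Visit 1 and Visit 5. So are the trauma narratives, the other free-text material. Dreams are the exception.

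**4. Comparing the intervals.** MRI change is the Visit 5 value minus the Screening or Visit 1 value. The matching dream change is the Visit 5 score minus a score at day 0, and that second term is not scheduled. The longest scheduled interval, if the optional month-3 diary is obtained, runs from day 91 to day 365: 365 − 91 = 274 days, and 274/365 = 75% of the MRI interval. The first 91 days (25%) have no earlier point to compare with. Under Table 3 alone there is one collection and no interval.

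**5. What can be computed.**

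| Quantity | Table 3 only | With follow-up diaries |
|---|---|---|
| Arm difference in dream score at 1 year | yes | yes |
| Change during treatment | no | yes, from month 3 |
| Change from baseline, or improvement within an arm from baseline | no | no |
| Association of dream change with MRI change over the MRI interval | no | no |

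**6. The scale.** The hypothesis names DREAMS-C. The Dream diary section names SCORS-G and LIWC, and Table 8 names SCORS-G. This is a separate inconsistency and is not evidence about timing.

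**The case against.** The strongest reply is that a diary is a running record. The timing sentence may then be a hand-in rule, with the single mark at Visit 5 as the last date for returning it. On that reading text and table agree, entries could span the year, and the stated aim of assessing changes makes sense. This partly stands. The article gives no start date for entries, so early entries are not excluded. But it does not provide for pre-treatment entries either, and an unscheduled early entry is not a baseline that every patient will have. The abstract's promise of full clinical characterisation at baseline does not fill the gap, since it does not mention dreams. Nor does the psychoanalytic interview at Screening or Visit 1, which is not described as collecting or scoring dreams.

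A second reply is that randomisation protects the comparison between arms. This stands. With balanced arms in expectation, the difference in mean one-year scores estimates the same arm effect as the difference in mean change.

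A reader might therefore go too far in two ways. One is to infer that dream change cannot be measured at all. The documents do not support that, because diaries at months 3, 6, 9 and 12 would describe change during treatment. The other is to infer that the endpoint comparison is badly imprecise. The article gives no correlation between baseline and one-year dream scores, so the loss cannot be sized. With equal variances, a change score has 2(1 − r) times the endpoint variance. At an assumed r of 0.3 that is 2 × 0.7 = 1.4 times, which is worse than the endpoint alone; at an assumed r of 0.6 it is 2 × 0.4 = 0.8 times. What is forgone is adjustment for a baseline covariate, and its value is unknown.

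A third reply is that dreams are one of three measures in one secondary hypothesis, and that neither the power statement nor the primary analysis uses them. This stands and limits the weight of the point.

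**Conclusion.** The point holds in a bounded form. The article states a schedule that cannot deliver part of a stated hypothesis, and this is a mismatch within the article, not a detail left to a fuller document. No pre-treatment dream score is scheduled for any of the 60 randomised patients. Change from baseline, within-arm improvement and the association with MRI change over the MRI interval are therefore out of reach for dreams. The randomised contrast at one year stays valid, and change during treatment can be described where follow-up diaries exist.

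The conclusion rests on the schedule as written: one mark in Table 3, and text that reaches back no further than the follow-up points. If dated pre-treatment entries are in fact required elsewhere, the article needs only to say so. The primary MRI outcomes and the other two measures in the hypothesis are unaffected. This should be fixed, but it does not threaten the trial's main result.

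**What to change.** - **Baseline diary.** Schedule a self-completed dream diary in the Screening/Visit 1 window, over a fixed span, finished before the arm is communicated. Repeat it over the same span at Visit 5, so that both ends match the MRI interval.
- **Timing.** Bring Table 3 and the Dream diary section into agreement on whether the 3-, 6- and 9-month collections are required, optional or dropped.
- **Scale.** Name one scale for the hypothesis: either score the diaries with DREAMS-C and describe it in the methods and Table 8, or rewrite the hypothesis for SCORS-G.
- **Patients already enrolled without a baseline diary.** Restate the dream hypothesis as a between-arm difference at one year, and drop the association of dream change with MRI change.

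The cost is modest, though it is more than one added mark in the table. Depressed patients take on a further baseline task, and there is a second set of diaries to score. The Randomization section communicates the arm on the same day as the included patient's ID is sent, so the diary must be complete before that step. The baseline MRI is already placed before randomisation, and the diary can use the same window.
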